# 1. Introduction

## 1.1 Background

### 1.1.1. *COVID-19 infection*

The first report of infection with COVID-19 occurred in Wuhan, China, in late 2019. Since that time, there have been multiple millions of reported cases across the world with a range of severity, several thousand deaths and documented sustained human-human transmission. On January 30th 2020, the World Health Organization (WHO) declared this outbreak a Public Health Emergency of International Concern. Given past history with novel coronaviruses, such as Severe Acute Respiratory Syndrome (SARS) and Middle East respiratory syndrome coronavirus (MERS-CoV), public health agencies have responded aggressively to the urgent need to acquire knowledge regarding this emerging infection. An important component of this urgently needed knowledge includes understanding the effectiveness of alternative treatment strategies in patients with suspected or proven infection.

Estimates of the burden of critical illness among patients infected with COVID-19 vary, with estimates of case-fatality and proportion of patients who become critically ill being unstable. Several factors contribute to this uncertainty including differential timing between diagnosis and development of critical illness or death, the true incidence of infection being uncertain because of possible under-reporting of asymptomatic or mild cases, the sensitivity of diagnostic methods, possible limitation on the number of diagnostic tests that can be performed, and changing case-definitions.

### 1.1.2. *ACE2 as the 'entry' receptor for SARS-CoV-2 infection*

Receptor recognition is the first step of a viral infection and is a key determinant of host cell and tissue tropism. The metalloproteinase angiotensin-converting enzyme 2 (ACE2) has been identified as the functional entry receptor for SARS-CoV-2, similar to SARS-CoV (Walls et al., 2020). ACE2 is expressed on lung alveolar epithelial cells and enterocytes of the small intestine and it is present in arterial and venous endothelial cells and arterial smooth muscle cells (Hamming et al., 2004). SARS-CoV-2 has a Spike protein that harbors a furin cleavage site at the S1/S2 boundary, which can be processed by the host cellular protease TMPRSS2, in turn modulating the Spike protein such that it can then bind to ACE2, allowing the SARS-CoV-2 virus to enter the cell (Hoffmann et al., 2020; Walls et al., 2020).

The fact that SARS-CoV-2 binds with ACE2 receptors might explain why COVID-19 pathology is predominantly a disease of the alveoli - where ACE2 is widely expressed (Hamming et al., 2004; Li et al., 2020) – often resulting in acute respiratory distress syndrome (ARDS). The virus-induces a strong proinflammatory response that results in endothelitis which affects multiple organs (Varga et al., 2020) and results in vascular and thrombotic complications such as vascular leakage and micro-thrombosis. Similar to the pathological lung changes observed with SARS, these potentially ACE2-mediated pathophysiological features are already present at an early disease stage within the first 10 days (Gu and Korteweg, 2007) and provide a rationale to target ACE2 entry and interaction with the virus early.

### 1.1.3. *ACE2-deficiency and kinin-kallikrein activation*

With respect to the kinin-kallikrein system there is a clear role for ACE2. Bradykinin (BK) is a linear nonapeptide that is formed by the proteolytic activity of kallikrein on kininogens (Bhoola et al., 1992). Kallikreins are serine proteases and can be divided in plasma kallikrein and tissue kallikreins. The plasma and tissue kallikreins release the vasoactive peptides known as kinins, which cause relaxation of vascular smooth muscle and increased vascular permeability (Bhoola et al., 1992; Marceau et al., 2018). Plasma kallikrein processes high-molecular-weight kininogen (HMWK produced by the liver) into bradykinin, while tissue kallikrein processes low-molecular-weight

kininogen (LMWK produced by the liver) and results in Lys-BK (29802875). These are the ligands for the constitutively expressed bradykinin receptor B2 on endothelial cells. In addition, the enzymes (carboxypeptidase M (CPM) and carboxypeptidase N (CPN)) can further process BK and Lys-BK into des-Arg9-BK and Lys- des-Arg9-BK respectively, which are ligands for bradykinin receptor B1, a receptor on endothelial cells that is upregulated under proinflammatory conditions (Marceau et al., 2018). These kinins have strong vasopermeable and vasodilatory capacity and are tightly controlled to prevent excessive angioedema (Marceau et al., 2020). ACE and ACE2 both have roles in inactivating the ligands for the bradykinin receptors (Gralinski et al., 2018). ACE mainly inactivates bradykinin which is the major ligand for B2 receptors, while ACE2 does not inactivate bradykinin, but can inactivate des-Arg9-BK, which is a potent ligand of the B1 receptor in the lung and can be upregulated by inflammation (Hess et al., 2017; Sodhi et al., 2017). In this way, ACE2 can be protective against pulmonary edema, especially in the setting of inflammation (Imai et al., 2005). Therefore, ACE2 deficiency could lead to impaired inactivation of the B1 ligands locally in the lung, triggering a cascade that leads to vascular leakage, activation of zymogen systems such as plasma kallikrein, promoting B2 signaling and activation of the contact system [figure 1]. Such a cascade would lead to elevation of D-dimers and microthrombosis, both of which are commonly reported in COVID-19 disease (Fox et al., 2020; Poor et al., 2020; Xu et al., 2020).

[figure not shown]

**Figure 1. Conceptual model of SARS-CoV-2 interaction with ACE2 receptor and proximate downstream signaling.** SARS-CoV-2 reaches the alveolus. The spike protein is transformed by the host serine protease TMPRSS2, allowing the virus to bind to ACE2. ACE2 expression is downregulated resulting in ACE2 deficiency locally. This will result in the incapacity to neutralize B1 ligands, especially des-Arg9-BK leading to plasma leakage. Inflammation will increase the expression of Bradykinin 1 receptor (B1R), increasing the plasma leakage. Plasma leakage will then contribute to B2R activation, maintaining vascular leakage and activating the contact system in the subendothelial space, with d-dimer leakage into the circulation. The virus has now the option to infect local endothelial cells, causing endothelitis, which can continue into the larger blood vessels. An uncontrolled continuation of this status will result in microthrombosis and eventually in fibrosis.

#### 1.1.4. Potential strategies to block ACE2-deficiency-mediated kinin-kallikrein activation.

The kinin-kallikrein system could be explored as a possible treatment target. Blocking the bradykinin receptors (B1R and B2R) would be a strategy. However, there are currently no available B1R blockers. Two drugs are commercially available to target these symptoms. A B2R blocker, icatibant (Firazyr®), is approved for the treatment of patients with hereditary angioedema (HAE) and ACE inhibitor

induced angioedema (Dubois and Cohen, 2010). And an anti-kallikrain monoclonal antibody lanadelumab that is approved for the prevention of HAE. Given the abundance of the plasma leakage resulting in activation of B2 receptors at the site of infection (Imamura et al., 2005; Sodhi et al., 2017; Taylor et al., 2013), there is a sound scientific rationale to explore lanadelumab as immune modulatory strategy in patients with moderate and severe COVID-19 disease.

## 1.2 Rationale for the current study

In a proof-of-concept study in patients with COVID19 disease we have demonstrated the involvement of the kinin-kallikrain system.

To support the rationale to target the kallikrein-kinin system in COVID-19, we investigated whether we could identify active plasma kallikrein (PKa) in the plasma of patients. Plasma prekallikrein (PK) needs to be cleaved into its active form that in turn will result in formation of bradykinin. All patients with severe COVID-19 showed a lower concentration of uncleaved PK, with a concomitant significant higher concentration of PKa compared to healthy volunteers. All patients with COVID-19 had a significant increased PKa compared to healthy controls (Figure 2). These data support the concept of an increased activation of the plasma kallikrein-kinin system in patients with COVID-19.

[figure not shown]

Figure 2: Prekallikrein (PK) and kallikrein active fragments (PKa) in plasma of 20 patients with COVID-19 and ten healthy volunteers. (A). Western blots showing prekallikrein (PK) and active plasma kallikrein fragments (PKa) in the plasma of healthy volunteers, (B) 10 patients with COVID-19 admitted on the ward, and (C) 10 patients with COVID-19 admitted to the ICU. (D). Intact PK and (E) PKa fragments quantified by using dextran activated samples of a normal pool plasma to create a standard curve. EDTA-plasma samples from healthy volunteers and COVID-

patients were related to this standard via linear regression. Statistics were performed by one-way ANOVA with Dunnett multiple comparison test.  $P < 0.05$  was considered significant.

Therefore, lanadelumab, given its mechanism of action coupled with the available literature, and anecdotal reports of icatibant use in COVID-19, provides a reasonable rationale for the study proposed which seeks to evaluate the efficacy and safety of lanadelumab to reduce/prevent acute respiratory distress syndrome associated with COVID-19 pneumonia.

Ad 2. In the registration package, PK/PD properties of lanadelumab have been well characterized in healthy volunteers and HAE patients (aged between 12 to 75 years old), following 300 mg q2w SC administration (approved dosage for HAE indication). The characterization conducted using a

population PK/PD modeling and simulation approach showed that the 300 mg q2w SC with approximately 15 days half-life provides sufficient exposure for HAE efficacy with well-demonstrated safety profiles. Following SC administration of 300 mg q2w, the Cmax was approximately 34 ug/mL and the Tmax was 4 days or longer, which may not be sufficient to meet the early treatment needs (regarding the rate and extent of SC absorption) in patients with progressing disease of COVID-19 pneumonia. Rapid progression of pulmonary deterioration from early clinical symptoms to severe in patients admitted into the hospital clearly demonstrates the need for rapid, high, and safe exposure of effective medicines. IV administration of lanadelumab is expected to meet such a need and 300 mg IV will provide much earlier Tmax and higher concentrations in the earlier PK phase compared to 300 mg SC administration. Although the sponsor has not tested the IV route of administration in the HAE clinical package, the exposure to lanadelumab following an IV administration of 300 mg (predicted Cmax: 94.1 ug/mL) assuming 66% SC bioavailability) is expected to be comparable to observed exposure in the clinical HAE package, and the nonclinical package. Therefore, the sponsor selects IV administration for the proposed clinical pharmacology study.

In the pop-PKPD document [attached as supplemental file] extensive information is provided why the intravenous administration is preferred over the subcutaneous administration.

Finally, in the next paragraphs information on safety of lanadelumab will be outlined further supporting the need for this drug in COVID-19 disease.

#### Biological information for lanadelumab

Lanadelumab (Takhzyro®, formerly DX-2930 or SHP643) is a recombinant, Chinese hamster ovary (CHO) cell expressed, fully human immunoglobulin G subclass 1 (IgG1), kappa light chain, monoclonal antibody. Lanadelumab is a potent and specific inhibitor (inhibition constant [Ki]=0.12 nM) of the proteolytic activity of active plasma kallikrein (PKa) (Kenniston et al., 2014). Lanadelumab has been approved by the FDA and EMA for the prophylactic treatment in patients with type I or II hereditary angioedema (HAE), a rare and life-threatening disease (Longhurst and Cicardi, 2012). The activity, potency, and specificity of lanadelumab have been demonstrated in vitro and ex vivo. Preclinical, in vitro pharmacology potency studies indicated that PKa inhibition in rat and cynomolgus monkey (Ki of 170 pM and 69 pM, respectively) was similar to human PKa inhibition (Ki of 125 pM) (Busse et al., 2018; Kenniston et al., 2014). Lanadelumab possesses high specificity for PKa and does not inhibit 20 other serine proteases tested at concentrations of either 1 or 5 µM, including activated factor XI, which has significant homology to PKa. In an in vivo model of edema, lanadelumab inhibited the induction of paw edema in rats in a dose-dependent manner.(Kenniston et al., 2014) Lanadelumab does not have adverse effects on vital functions of the central nervous system (CNS), cardiovascular (CV) system, or respiratory system based on safety pharmacology endpoints incorporated in the pivotal repeat-dose studies in rats and cynomolgus monkeys ([https://www.ema.europa.eu/en/documents/assessment-report/takhzyro-epar-public-assessment-report\\_en.pdf](https://www.ema.europa.eu/en/documents/assessment-report/takhzyro-epar-public-assessment-report_en.pdf)).

In non-clinical studies, the pharmacokinetics of lanadelumab exhibited low clearance, low volume of distribution, and long half-lives (rats approximately 3 days on average and cynomolgus monkeys approximately 10 days on average), with an approximate subcutaneous (SC) bioavailability of 66% in cynomolgus monkeys.(Kenniston et al., 2014) Maximum concentrations following SC administration were reached 1 to 4 days and 2 to 4 days post dose in rats and cynomolgus monkeys, respectively. The nonclinical toxicity studies demonstrated that SC administration of lanadelumab to rats (28 days) and cynomolgus monkey (up to 6 months) was well tolerated with no evidence of organ toxicity at weekly doses of up to and including 50 mg/kg, the highest dose administered and the no-observed-adverse-effect-level (NOAEL) in all nonclinical studies. At the NOAEL in the 6-month cynomolgus

monkey study, exposure margins based on maximum concentration occurring at  $t_{\max}$  ( $C_{\max}$ ) and area under the drug concentration-time curve (AUC) were approximately 21- and 23-fold higher, respectively, than those observed at the clinical dosage of 300 mg every 2 weeks (q2wks; DX-2930-03) ([https://www.ema.europa.eu/en/documents/assessment-report/takhzyro-epar-public-assessment-report\\_en.pdf](https://www.ema.europa.eu/en/documents/assessment-report/takhzyro-epar-public-assessment-report_en.pdf)).

The clinical development program for lanadelumab consists of one pivotal study supported by interim data from a long-term open label extension study and data from a “proof-of concept”/dose-finding study (Banerji et al., 2017, 2018; Riedl et al., 2017). Choice of lanadelumab dosing for the pivotal phase 3 (HELP) study was accomplished by the sponsor using the safety, pharmacokinetic and pharmacodynamic data generated in the phase 1 studies DX-2930-01 (healthy subjects) and DX-2930-02 (subjects with HAE). The planned range of lanadelumab dosing for the clinical development program was based upon estimation of the level of plasma kallikrein (pKal) inhibition necessary to attain effective prophylaxis against HAE attacks. It was hypothesized that the necessary molar concentration of lanadelumab would correspond to the average  $C_{\max}$  attained following administration of ecallantide, a biologic pKal inhibitor. The  $C_{\max}$  obtained following ecallantide administration is approximately 80 nM or 586 ng/mL.

The pivotal study, DX-2930-03, was a phase 3, multicenter, randomized, double-blind, placebo-controlled HAE prevention study with a 26-week long treatment duration. One hundred and twenty-five subjects (115 adults and 10 adolescents aged 12-≤18) were included in study DX-2930-03 and treated with placebo (N=41) or lanadelumab (N=84). Among the adolescents, 4 were treated with placebo and 6 received lanadelumab. (Banerji et al., 2018) The main eligibility criteria were subjects ≥12 years of age with HAE and at least 1 investigator confirmed HAE attack per 4 weeks. The number of investigator- confirmed HAE attacks during the treatment period was reduced in all lanadelumab treatment arms compared to placebo ( $p < 0.001$  for all lanadelumab arms vs placebo). The relative risk reduction compared to placebo ranged from 73% in the 300 mg every 4 weeks arm to 87% in the 300 mg every 2 weeks arm, corresponding to a decrease of approximately 1.5 attack/4 weeks in the 150 mg q4wks and 300 mg every 4 weeks arms and 1.75 attacks/4 weeks in the 300 mg every 2 weeks treatment arm based on LS mean HAE attack rate in the four treatment arms.

In summary of the above:

We believe lanadelumab is the drug of choice over icatibant to be deployed in prevention of ARDS in patients with COVID-19 disease. We have chosen the intravenous route of administration over the licensed subcutaneous route for direct clinical effect. We believe this approach is safe.

#### Timing of drug administration (target population)

The main goal of treating patients with moderate COVID-19 disease in the hospital is to prevent the progression to severe disease that frequently progresses to ARDS and requires prolonged mechanical ventilation. We plan to include patients with moderate or severe disease for treatment with lanadelumab according to the SWAB definition for COVID-19 disease. Treating patients who are hospitalized with respiratory symptoms as early as possible with a dosing regimen above will optimize our ability to test modulation of the kallikrein/kinin pathway as potential treatment strategy in patients with COVID-19.

**1.3 Primary objectives**

- To deliver the proof-of-concept of relieve of symptoms by using lanadelumab in patients with moderate to severe COVID-19 disease
- To demonstrate the safety of lanadelumab given as intravenous administration in patients with COVID-19 disease.

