| Objective(s)                                        | 
The primary objectives of this study is as follows:
 
 
• To generate the proof of concept for lanadelumab for treatment of symptoms moderate to severe patients COVID-19 disease
 
• To demonstrate its safety after intravenous administration.
 
                                                                                                                                                                                                                                                                                                                                                                                                                                                                                                                                                                                                                                                                              |
| Rationale                                           | 
So far little is very few drugs have demonstrated positive results for treatment of COVID19.
 
Recently we have shown that the use of icanatibant in COVID-19 results in a potent decrease in oxygen use. Yet the effect of the three dosages as according to the label dose was insufficient to maintain the clinical improvement in a small group of patients. We argue that with the use of lanadelumab a more lasting effect can be reached due to its longer half life.
                                                                                                                                                                                                                                                                                                                                                                                                                                                                                                   |

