|---------------------------------------------------|-------------------------------------------------------------------------------------------------------------------------------------------------------------------------------------------------------------------------|
| Bioanalysis                                | Plasma concentrations of lanadelumab will be performed via Takeda through the commercial lab that has performed sample measurements in their clinical trial.                                                            |
| Pharmacokinetics                           | Non-linear mixed effect modelling will be deployed by the department of Pharmacy and the Radboud Applied Pharmacometrics group.                                                                                         |
| Safety and
demographics                | Tabulation and descriptive statistics for subject characteristics. Tabulation of adverse events, vital signs and biochemistry and haematology data.

Statistical evaluation will be supervised by [name]. |

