## 2. Study design

The proposed study is an open-label, randomized, intervention study in patients tested positive for SARS-CoV2 on the ward. Forty patients will be enrolled in a 1:1 randomized fashion for intervention (Ivanadelumab administration) versus controls (standard treatment). To be able to randomize forty patients within the study duration, a multi-center approach is chosen.

We have chosen to perform this trial in patients that are Sars-COV2 positive as we believe they can directly benefit from this intervention. As such it merits preference over testing this drug first in healthy volunteers to demonstrate the safety of intravenous administration and then move into patients with COVID19 disease. We argue this is best done in a combined fashion.

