### 5.3 Method of assigning subjects to treatment groups

Subject will be randomized in a 1:1 ratio to receive lanadelumab or standard clinical management without drug intervention. Each group will contain 20 participants.

Randomization will be done by Castor. Each patient will be entered into the Castor system and randomization will be allocated immediately. This is a standard procedure as deployed in other trials.

Each site has drug on site for at least one patient and therefor randomisation to the intervention arm can be acted upon immediately. Considering the small sample size there will be no stratification.

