## **7. Data analysis**

### **7.1 Sampling design and sample size justification**

This is pragmatic study to deliver a proof of concept on the use of lanadelumab in COVID patients on the ward. No formal sample size has been performed.

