### **7.3 Statistical analysis**

Statistical analysis will be performed using descriptive statistics for tabulation of population as well as results. [name] from our department of health evidence will help with the statistical analysis. Appropriate test will be deployed.

For the primary endpoint we intend to collect repeated measurements of oxygen use in L/min and therefore any significant decline in a patient's health should be reflected in these repeated measurements. We acknowledge that missing data due to death is a potential source of bias, particularly if oxygen is stopped at the point where a significant decline is observed. Therefore, a worst-case scenario sensitivity analysis, in which the highest value of oxygen recorded for any patient is imputed for patients with missing data following their death. Other valid methods to account for missing data due to death will be investigated and included in the Statistical Analysis Plan.

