#### 9.1.4 *Benefits and risks assessment, group relatedness*

For a number of reasons administration of the intravenous lanadelumab can lead to problems with administration. Pharmacokinetic properties and information about safety have only been derived from modelling and simulation.

There are currently no treatment options for patients with COVID19. As lanadelumab subcutaneous is expected to result in a substantial delay in effect due to the slow absorption, intravenous administration is important. Therefore, we want to investigate this alternative safe method to administer lanadelumab. The potential value of this research is to provide both the proof of concept as well as safety of treatment in COVID disease..

This study will be performed in patients with COVID disease as recommended by the guidelines for bioequivalence. Lanadelumab is well tolerated in other patient cohorts. There is a mild side effect profile as also

demonstrated in large phase III trials. Moreover, to limit the risk of side effects, this study is designed as two dose study.

The study participants are subjects  $\geq 18$  years. The safety and efficacy of intravenous lanadelumab in children and adolescents aged less than 18 years have not yet been established.

For pharmacokinetic purposes and safety assessment, blood samples will be collected. The total blood volume taken will be approximately 100-150 mL. During the days that blood samples will be collected for biomarker and PK-information, an intravenous cannula will be inserted to facilitate blood sampling and limit the amount of venous punctures.

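### A primary objective is to demonstrate the safety of intravenous lanadelumab, but 20 treated patients can only describe it: with no event in 20, true rates up to about 14–17% remain possible

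*Protocol*

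**What the plan says.** Section 1.3 lists two primary objectives. The second is "To demonstrate the safety of lanadelumab given as intravenous administration in patients with COVID-19 disease". The objectives row of the synopsis has the same aim: "To demonstrate its safety after intravenous administration". Section 9.1.4 repeats it as the purpose of the work: "The potential value of this research is to provide both the proof of concept as well as safety of treatment in COVID disease".

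On size, section 5.3 states "Each group will contain 20 participants", so 20 patients are dosed. The synopsis describes the number as empirical and the study as hypothesis-generating. Section 7.1 states "No formal sample size has been performed", and section 3.6 calls the study explorative.

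On analysis, the synopsis plans "Tabulation of adverse events, vital signs and biochemistry and haematology data". Its row on safety, demographics and statistics says that, in general, subjects who completed the study enter the safety evaluation, and it allows exclusions, for example after incorrect administration. The same row also says that patients count as evaluable once the first dose is given, whereas section 3.5 requires both treatment days.

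**The concern.** To demonstrate safety is a confirmatory claim: it says the data will be able to rule out harm at a rate that matters. The protocol's own description of the study, hypothesis-generating with an empirical size, does not support such a claim.

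The number of dosed patients is fixed in the protocol, and no later analysis document can make 20 patients informative about uncommon reactions. The gap matters because section 1.2 says the intravenous route was not tested in the hereditary angioedema clinical package. Readers will therefore look to this trial for information on intravenous use. If the objective stands, the report has to answer whether safety was demonstrated, and the design does not allow a sound yes.

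**Working it through.** The protocol gives no power, precision or tolerated event rate for safety, so there is no stated figure to reproduce. The check asks what 20 treated patients can establish.

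**Inputs**
- Treated patients: n = 20 (sections 3.1 and 5.3).
- Reference rates from subcutaneous use (section 4.3): hypersensitivity 1%, raised liver enzymes 2%.
- Confidence level: 95%, one-sided and two-sided. This is my assumption, as the protocol gives none.

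**1. What no events in 20 rules out.** The exact upper limit for 0 of n is 1 − α^(1/n) one-sided and 1 − (α/2)^(1/n) two-sided.
- One-sided: 1 − 0.05^(1/20) = 13.9%.
- Two-sided: 1 − 0.025^(1/20) = 16.8%.
- Cross-check by the rule of three: 3/20 = 15.0%.

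With one event in 20, the two-sided upper limit is the 97.5th percentile of Beta(2, 19), which is 24.9%.

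**2. Chance that a real reaction goes unseen.** P(no event in 20) = (1 − p)^20.

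| True rate p | P(no event in 20) | P(at least one) |
|---|---|---|
| 1% | 0.99^20 = 81.8% | 18.2% |
| 2% | 0.98^20 = 66.8% | 33.2% |
| 5% | 0.95^20 = 35.8% | 64.2% |
| 10% | 0.90^20 = 12.2% | 87.8% |

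**3. Effect of evaluating completers.** If fewer than 20 enter the safety evaluation, the limit after no events widens. The numbers of completers below are illustrative.

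| Evaluated | One-sided 95% limit | Two-sided 95% limit |
|---|---|---|
| 20 | 13.9% | 16.8% |
| 18 | 15.3% | 18.5% |
| 16 | 17.1% | 20.6% |

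The smaller n is the lesser problem. Patients who stop early may include those who reacted, so leaving them out can also remove events from the count. The arithmetic does not capture that.

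**4. Size needed for a tighter bound.** To exclude a rate u after no events, n must be at least ln(0.05)/ln(1 − u) one-sided, or ln(0.025)/ln(1 − u) two-sided. For u = 10% this gives 29 or 36 treated patients; for u = 5% it gives 59 or 72. This shows scale only and is not a proposal to enlarge the trial.

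The randomised and historical controls do not narrow any of these limits, which concern the rate in treated patients.

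**The case against.** The strongest reply is that the protocol is open about its nature. It calls itself hypothesis-generating and explorative, plans description, and says no size was calculated. On that view *demonstrate* is loose wording and the rest belongs in the statistical analysis plan. Much of this stands. The choice of test and any margin may properly sit in that plan, and their absence here is no fault. The objective and the number dosed, however, are fixed in the protocol and do not fit together.

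It can also be said that the completer rule applies only in general and that the same synopsis row makes patients evaluable after the first dose. That softens the rule, but section 3.5 then asks for both treatment days, so the safety set remains unsettled. The stopping rule and staggered entry in section 3.7 and the primate infusion data in section 4.3 reduce the risk to patients. They do not define when safety has been shown.

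Several stronger readings are tempting, and the documents do not support them:
- **An empty adverse event table is likely, and the protocol would call it proof.** No section says that absence of events will be read as safety. At the 6% dizziness rate in section 4.3, at least one case is expected with probability 1 − 0.94^20 = 71%. Only the 1% and 2% reactions, each taken singly, are likely to be missed.
- **The safety aim is the excuse for skipping a healthy-volunteer study.** The reason given in section 2 is direct benefit to patients. In "As such it merits preference over testing this drug first in healthy volunteers to demonstrate the safety of intravenous administration", the safety wording describes the step not taken.
- **This is the first human intravenous use.** The protocol does not say so. Section 1.2 limits its statement to the hereditary angioedema programme.
- **The trial lacks power to compare safety between arms.** No between-arm safety test is stated, and "Appropriate test will be deployed" in section 7.3 is not tied to safety. Any power figure would rest on assumed rates.

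**Conclusion.** The point holds as a mismatch between a primary objective and the size of the treated group. With 20 dosed patients and no events, true rates up to 13.9% (one-sided 95%) or 16.8% (two-sided 95%) stay open. A 1% or 2% reaction goes unseen about 82% or 67% of the time. The design can describe safety and exclude very frequent reactions, but it cannot demonstrate safety.

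The figures assume that all 20 patients are dosed and evaluated, that patients are independent, and that 95% is the chosen level. They become less favourable if only completers are evaluated. The 1% and 2% come from subcutaneous use and serve as reference points, not as estimates for the infusion. The trial can go ahead at its planned size; what needs to change is the stated claim and the safety set.

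**What to change.** 1. **Section 1.3 and the synopsis objectives:** replace the aim of demonstrating safety with *to describe the safety and tolerability of intravenous lanadelumab in patients with COVID-19*. Align the statement of the study's value in section 9.1.4.
2. **Synopsis (safety, demographics and statistics) and section 7.3:** add *Safety is evaluated in all patients who received any lanadelumab. For each event, the number and proportion of these patients are given with exact (Clopper-Pearson) 95% confidence limits.* State that the evaluability wording in section 3.5 does not define this set.
3. **Section 7.1:** add *If an event is seen in none of 20 treated patients, only true rates above about 14% (one-sided 95%) or 17% (two-sided 95%) are excluded.*
4. **No between-arm difference in adverse events as the protocol stands.** Section 6.3 records an adverse event only if study medication is reasonably suspected as its cause. Controls receive none, so their count would be close to zero by definition and the difference would be an artefact of recording. Such a comparison could be added only if that causality condition were removed and events were recorded alike in both arms.

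The cost is a few lines of text and one exact interval per event, with no added patients, visits or samples. The downside is a more modest safety claim.
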